### Blinding

The RCT will be a double-blind trial. All study personnel and participants will be blinded to the intervention, except for the surgeons and other operating theatre personnel, who do not have any other role in the study.

### Statistical methods

Treatment groups will be examined for comparability at baseline with respect to demographic and prognostic factors. An ITT analysis based on all the randomized individuals - for the efficacy measures - will apply. Comparisons between groups of the primary end point will include all repeated measures and be analyzed with the use of a mixed effects model, with random factors for participant and centre.

Clinically important or relevant difference for the KOOS_5_ and KOOS subscales were chosen as 10/100 points. Thus a confidence interval excluding differences greater than 10 units between groups will be interpreted as indicating the absence of a clinically meaningful difference. This means that, if the 95% Confidence Interval around the group mean difference does not include a *potential* clinical benefit of 10 KOOS points, then we will then consider the therapeutic strategies equal.

Patients in the sham group who, later during the course of the study, may have an APM procedure will, according to the ITT principle, still be analyzed in the group to which they were originally allocated. Secondarily, all analyses will be supported/interpreted in the context of the corresponding results according to the per protocol populations.

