### Sample size

The sample-size calculation is based on the assumed superiority of the arthroscopic procedures over the sham procedure. For a two-sample pooled t-test of a normal mean difference with a two-sided significance level of 0.05, assuming a common standard deviation (SD) of 15 in the KOOS_5_ score, a sample size estimation of the ITT population indicated that 36 individuals per group would be required to obtain a power of at least 80% to detect a minimal important change (MIC) of 10 KOOS_5_ score units. The MIC of 10 points and SD of 15 is based on findings from similar patient groups and interventions [19].

Following these estimations, it was decided to include 80 individuals in total (40 patients in each group), allowing for a 10% drop-out rate.

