## Discussion

Degenerative meniscus tears are common and related to the development of knee osteoarthritis [1,3-5]. Arthroscopic partial meniscectomy is the current treatment of choice in patients with mild or no concomitant knee osteoarthritis but this has not been formally evaluated in randomized placebo controlled trials.

The outcome of this study will show whether arthroscopic partial meniscectomy is a viable treatment modality. Inclusion of a sham surgery treatment will enable us to study the effect of the partial meniscectomy per se. The findings of this research will potentially be of international importance and will be readily translatable into clinical practice, irrespective of the results. If our results are in favor of APM, we will have evidence to support continued use of APM in this patient category. If, on the other hand, our results indicate that the efficacy of APM is less than placebo (and it may do more harm), then this would also significantly impact upon current practice and APM should not be the treatment of choice in middle-aged patients with an MRI-verified meniscus tear and mild or no knee osteoarthritis. No difference between APM and placebo might not be regarded as a strong enough piece of evidence to stop operating on middle-aged patients with meniscus tear and mild OA. However, a finding of superiority for arthroscopy would certainly increase the tendency to treat these patients surgically, and a finding of superiority for placebo would discourage operative treatment. Finding no effect of APM would support the notion that a degenerative meniscus tear is the first sign of future knee OA. If so, the treatment of choice should conform to treatment guidelines for mild and moderate knee OA.

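### The 10-point rule is stated once without direction and once on benefit alone, so a result that favours sham can be labelled equal

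*Protocol article*

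**What the plan says.** All references are to the protocol article.

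- **Statistical methods** sets 10 points out of 100 as the clinically relevant difference for KOOS5 and the KOOS subscales. It then says that "a confidence interval excluding differences greater than 10 units between groups will be interpreted as indicating the absence of a clinically meaningful difference". This sentence names no direction.
- The next sentence is offered as an explanation of that one. If the 95% CI around the group mean difference does not include a potential "clinical benefit of 10 KOOS points, then we will then consider the therapeutic strategies equal". This sentence mentions benefit only. It gives no lower bound and does not require the CI to include 0.
- **Purpose and hypothesis** frames the question as whether benefit is greater after APM than after sham surgery.
- **Discussion** considers superiority of arthroscopy, superiority of placebo and no difference as separate findings. No difference might not be strong enough evidence to stop operating, whereas "a finding of superiority for placebo would discourage operative treatment".
- **Sample size** plans "For a two-sample pooled t-test of a normal mean difference with a two-sided significance level of 0.05".

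**The concern.** The two sentences are presented as one rule, but they accept different sets of results. The first needs both CI limits inside -10 to +10. The second, if benefit means benefit of APM, needs only the upper limit to lie below +10. A CI that lies wholly below 0 always passes the second test, however far below 0 it lies, and the label attached is that the strategies are equal.

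The label matters. The Discussion regards a finding of no difference as weaker grounds for changing practice than a finding that placebo is superior. Calling a sham-superior result equal would move it into the weaker category. The rule also governs how the primary outcome is interpreted, so it should give one answer for any given CI before the data are seen.

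**Working it through.** **Inputs, all from Sample size.** The plan is "assuming a common standard deviation (SD) of 15" in KOOS5, a difference of 10, two-sided alpha 0.05, and "36 individuals per group would be required to obtain a power of at least 80" per cent. It decides to "include 80 individuals in total (40 patients in each group), allowing for a 10% drop-out rate".

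**The plan's own figure.** Normal approximation: n = 2 × (1.96 + 0.84)² × 15² / 10² ≈ 35.3, so 36 per group (power 80.7%). The exact pooled t-test needs 36.3, with 79.7% power at 36, which is close enough. Dropout: 36 / 0.90 = 40 per group, 80 in total. The sample size is not in dispute.

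**CI half-width.** Standard error = 15 × √(2/n); half-width = t(0.975, 2n − 2) × standard error.
- n = 36: standard error 3.54, half-width 7.05.
- n = 40: standard error 3.35, half-width 6.68.

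**The rules in terms of the observed difference d (APM minus sham), n = 36.**
- First sentence met when the CI is inside -10 to +10: |d| < 10 − 7.05 = 2.95.
- Second sentence, benefit of APM, met when the upper limit is below +10: d < 2.95.
- Sham significantly better when the upper limit is below 0: d < -7.05.

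The third region lies wholly inside the second. This is logic and holds at any SD or sample size: an upper limit below 0 is also below 10.

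**Example.** d = -10 gives a CI of -17.1 to -2.9. The second sentence returns equal. The first does not, because differences in favour of sham of up to about 17 points are not excluded.

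**How often the sentences disagree.** They disagree when d is at or below about -2.95. For n = 36 the normal approximation gives Φ(-2.95/3.54) ≈ 20% at a true difference of 0 and Φ(7.05/3.54) ≈ 98% at -10. Simulation of 400,000 trials per scenario, with the SD estimated in each trial, gave:

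| True difference | n per group | First sentence met | Second sentence met | Disagree | Sham significantly better |
|---|---|---|---|---|---|
| 0 | 36 | 59.2% | 79.6% | 20.4% | 2.5% |
| -5 | 36 | 27.4% | 98.7% | 71.3% | 28.6% |
| -10 | 36 | 2.5% | 100% | 97.5% | 79.7% |
| 0 | 40 | 67.6% | 83.8% | 16.2% | 2.5% |
| -5 | 40 | 30.6% | 99.3% | 68.7% | 31.3% |
| -10 | 40 | 2.5% | 100% | 97.5% | 83.8% |

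Every trial with sham significantly better was called equal by the second sentence and none by the first.

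**If benefit in either direction was meant.** The second sentence then reduces to the first-sentence column, and the example CI of -17.1 to -2.9 is not called equal.

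**The case against.** **Benefit may mean benefit of either strategy.** The second sentence introduces itself as a restatement, the first speaks of differences between groups, and the conclusion is about both strategies. This reading is possible and removes most of the conflict. The near-100% figures belong only to the APM-benefit reading. But the either-direction reading is not stated, and Purpose and hypothesis points to benefit of APM.

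**A significant difference would be recognised first.** The plan has a two-sided comparison, and the Discussion recognises placebo superiority. A reader might infer that the trial is bound to report equality in the face of proven harm. The documents do not support that, since nothing says the 10-point rule overrides a significant result. Equally, nothing places the superiority comparison ahead of the rule, so the conflict remains in the text.

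**The scenarios are selective.** A true difference of -10 is extreme. At 0, only 2.5 of the 20.4 percentage points of disagreement are trials with sham significantly better. In the other 17.9 points the CI includes 0 and its upper limit is below +10, so it is correct to say that a relevant benefit of APM is excluded; only the word equal goes too far. The percentages also come from an unadjusted t-interval, whereas the plan specifies a repeated-measures mixed model. Both points stand, so the figures are illustrative.

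**Two stronger inferences should not be drawn.** Read hyper-literally, a CI wholly above +10 also does not contain the value 10 and would be equal. The preceding sentence rules this out, and the evident intent is to exclude benefits of 10 or more. Nor is it an error that a CI spanning both 0 and +10 is given no label: that detail is commonly left to a statistical analysis plan, which is not shown here.

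**Conclusion.** The point holds in limited form. The Statistical methods section fixes a direction-free 10-point criterion and then restates it as a criterion on benefit alone that concludes equality. Taking benefit as benefit of APM over sham, any result with sham significantly better meets the second sentence. That contradicts the sentence before it and the Discussion's separate conclusion of placebo superiority.

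The logical part does not depend on the SD or the sample size. The frequencies (about 20% disagreement at a true difference of 0, about 97.5% at -10) rest on SD 15, 36 per group, normally distributed outcomes, an unadjusted t-interval and the APM-benefit reading. With 40 per group, the figure at 0 is about 16%. On the either-direction reading the sentences largely agree and what remains is a wording fault.

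**What to change.** Replace the two sentences with one rule on the 2-year APM minus sham 95% CI, stated to be read alongside the two-sided superiority comparison:

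- **CI wholly above or wholly below 0:** report a difference in that direction, and state whether differences of 10 or more are excluded.
- **CI includes 0 and lies wholly inside -10 to +10:** 'equivalent'.
- **CI includes 0 and only the upper limit is inside the margin (below +10, with the lower limit at or below -10):** 'no clinically relevant benefit of APM', not equal.

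Taking the position of 0 first keeps the categories from overlapping. Without that order, a CI of +1 to +9 would be both a difference in favour of APM and equivalent. At the planned half-width of about 7 such a CI would not be expected, but a more precise analysis could produce one.

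The cost is wording only, with no change to sample size, data collection or the model. The downside is that some results that would have been called equal receive a weaker or different label.

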### Treatment failure

No a priori criteria for cross-over are given. Should a patient contact the department because of unbearable symptoms they will be un-blinded and in case of having had placebo surgery they will be offered a new arthroscopy. These patients will be treated as cross-overs and still be included in the study. In case of the patient having had arthroscopic surgery in the first place the patient will be referred to the responsible surgeon who will be in charge of referring to further surgical or non-surgical treatment and/or investigation. Both patient groups will be asked to fill out a KOOS questionnaire at the extra visit and will continue to be followed at the follow-ups determined by the study protocol.”

## Discussion

Degenerative meniscus tears are common and related to the development of knee osteoarthritis [1,3-5]. Arthroscopic partial meniscectomy is the current treatment of choice in patients with mild or no concomitant knee osteoarthritis but this has not been formally evaluated in randomized placebo controlled trials.

The outcome of this study will show whether arthroscopic partial meniscectomy is a viable treatment modality. Inclusion of a sham surgery treatment will enable us to study the effect of the partial meniscectomy per se. The findings of this research will potentially be of international importance and will be readily translatable into clinical practice, irrespective of the results. If our results are in favor of APM, we will have evidence to support continued use of APM in this patient category. If, on the other hand, our results indicate that the efficacy of APM is less than placebo (and it may do more harm), then this would also significantly impact upon current practice and APM should not be the treatment of choice in middle-aged patients with an MRI-verified meniscus tear and mild or no knee osteoarthritis. No difference between APM and placebo might not be regarded as a strong enough piece of evidence to stop operating on middle-aged patients with meniscus tear and mild OA. However, a finding of superiority for arthroscopy would certainly increase the tendency to treat these patients surgically, and a finding of superiority for placebo would discourage operative treatment. Finding no effect of APM would support the notion that a degenerative meniscus tear is the first sign of future knee OA. If so, the treatment of choice should conform to treatment guidelines for mild and moderate knee OA.

The study design has some limitations. The surgeon’s level of experience may differ since we need to allow general orthopedic surgeons to operate and not only sports surgeons. However, this has the benefit of an increased external validity. The population in the study is somewhat heterogeneous, from patients with no osteoarthritis to patients with mild osteoarthritis. We do not know whether a meniscus tear has different etiology in those with and without radiographic OA and how this may affect the result. There is no consensus on what defines a symptomatic meniscus tear or whether or not to perform an MRI before surgery. Clinical tests (McMurray, Apley, etc.) have not been proven to diagnose a meniscus tear accurately [34]. Therefore in this study, we included patients with knee pain and an MRI-confirmed medial meniscus lesion but there is a risk that, in some patients, symptoms may actually not be caused by the meniscus tear. Further, other patients who would otherwise have undergone a knee arthroscopy may be excluded due to the MRI not confirming a suspected meniscus tear. Another limitation of using MRI as a diagnostic tool is the risk of a false positive result. If the patient will be randomized to a sham operation, this error will never be discovered. We chose not to perform a diagnostic arthroscopy in the sham group primarily to reduce the risk of deep infection which we find would be unacceptable for a sham intervention. Other reasons were to avoid any accidental osteochondral lesions from the arthroscope and unwanted intervention from the surgeons.

The study does not include an activity score. A literature search revealed a lack of valid self-reported instruments of activity level for this diverse middle-aged population of varying physical activity levels. Since providing patients with accelerometers was not an option due to logistic reasons, we have not included any measure of activity level in this trial.

In spite of the above limitations, this study has strong methodological rigor through its design as a double-blinded placebo controlled RCT, compared to the earlier non-controlled studies of degenerative medial meniscus tears.

Ethical considerations are important when performing a surgical placebo controlled study. One may ask, ‘Is it ethical to perform placebo-controlled RCTs of surgery?’ since the initial precept in medicine is “First, do no harm”. An equally valid question though, may be, ‘Is it ethical not to perform placebo-controlled RCTs within orthopedics [35] and instead, potentially perform under-researched operations which may not benefit the patient, or worse, do harm?’

A recent study of vertebroplasty [36,37] has effectively shown how a placebo-controlled surgical trial can evaluate a given procedure that has been adopted widely despite an absence of robust evidence. Currently, there are three reasons to perform yet another placebo-controlled arthroscopy study, in addition to the one performed by Moseley and collaborators (2003). Firstly, the current study will focus on younger patients; secondly, these patients are at an earlier stage of disease and have not yet developed severe knee OA; and thirdly, a replication study is required to make Moseley’s evidence more convincing.

## Abbreviations

OA: Osteoarthritis; APM: Arthroscopic partial meniscectomy; RCT: Randomized controlled trial; KOOS: Knee injury and osteoarthritis outcome score; PRO: Patient-reported outcome; QOL: Quality of life
